### Sample size

The sample size was calculated based on the EASI_50_ achievement rate at week 4, which was defined as the proportion of patients who achieved ≥50% improvement in Eczema Area and Severity Index (EASI) score from baseline to week 4. According to preliminary observation data, we assume that the EASI_50_ achievement rate at week 4 would be 85% in the treatment group and 50% in the control group. Based on a 2:1 randomization ratio, the sample size is calculated with PASS 15.0 software. Setting a two-tailed *α* level at 0.05 and statistical power at 80%, the calculation yields a requirement of 40 patients for the treatment group and 20 for the control group. Considering a 10% dropout rate, the final enrollment target is set at 44 patients for the treatment group and 22 patients for the control group. The specific formula for calculating sample size was as follows:
$$n_{2}=\frac{\frac{p_{1}\times (1-p_{1})}{k}+p_{2}\times (1-p_{2})}{{\left(p_{1}-p_{2}\right)}^{2}}\times {\left(\mu_{\alpha /2}+\mu_{\beta }\right)}^{2},n_{1}=k\times n_{2}$$

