### Interventions

Patients in the treatment group will take a daily bath using MSS for a period of 4 months. To ensure the proper application of MSS, dermatologists will advise patients to first moisten their entire body with warm water, then apply 8 g of the product (4 g per press) to the skin surface. Massage gently for 3 to 5 min to ensure full absorption, and followed by rinsing with warm water. Patients in the control group will also take a daily bath using MSS placebo for a period of 4 months. The MSS placebo was formulated to be devoid of any Chinese herbal constituents, containing only the base excipients. It was manufactured by the same entity to guarantee perfect consistency with the active treatment in all physical attributes—appearance, weight, color, odor, and packaging. The guidance and application of MSS placebo in the control group will be identical to that for the treatment group.

In this study, both of patients in the treatment group and control group will receive the same foundational therapeutic regimen. The foundational therapies include desonide cream for mild AD and triamcinolone acetonide cream for moderate AD, both of which will be applied twice daily for 2 weeks. Additionally, all patients will receive urea ointment twice daily for 4 weeks. In this study, no additional treatment is permitted, and emergency interventions require documentation in detail and will result in the withdrawal of participation.

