### Outcomes

#### Primary outcome

The primary outcome indicator in this study is the EASI_50_ achievement rate at week 4. The EASI_50_ achievement rate is defined as proportion of patients achieving ≥50% improvement in EASI score from baseline to week 4.

The EASI score encompasses two main components: the affected body surface area (BSA) score (A) and clinical features score (B) for areas including the head and neck, trunk, upper limbs, and lower limbs (22). Component (A) evaluates the percentage of affected BSA for each area, which is scored on a scale of 0 to 6, as follows: 0 (0%), 1 (<10%), 2 (10–19%), 3 (20–49%), 4 (50–69%), 5 (70–89%), and 6 (90–100%). Component (B) assesses four critical clinical features: erythema (E), edema/papules/infiltration (I), excoriation (Ex), and lichenification (L). Each feature is scored based on severity, ranging from 0 to 3 points (0 = none, 1 = mild, 2 = moderate, 3 = severe). The overall EASI score is calculated by multiplying the product of (A) and (B) by regional weighted coefficients (ranging from 0.1 to 0.4) and summing these values across all regions. The total EASI score ranges from 0 to 72 points, with higher scores indicating greater severity. Based on the EASI score, the skin lesion condition of AD patients is categorized as mild (0–7 points), moderate (8–21 points), or severe (>21 points). In this study, the EASI score will be assessed at baseline (week 0), and at weeks 1, 2, 4, and 16.

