### Statistical analysis

In this study, data analysis will be conducted using the SAS 9.4 statistical software. Normally distributed quantitative variables will be summarized as mean and standard deviation (SD), while skewed distributions will be represented by the median and interquartile range (IQR). For inter-group comparisons of quantitative variables with normal distribution, the Student *t*-test will be utilized, whereas the Wilcoxon rank-sum test will be applied for skewed quantitative data. Repeated measurement data will be analyzed using repeated measures analysis of variance. Categorical variables will be presented as frequencies and proportions (%), with differences between groups evaluated through chi-square tests or Fisher’s exact tests.

Data analysis in this study will follow the intention-to-treat (ITT) principle, including all randomized participants regardless of adherence to the protocol or completion of the study (28). Missing data will be addressed under the missing-at-random assumption using sequential regression multiple imputation, which estimates missing values based on regression models that consider the relationships among all other variables (29). Furthermore, analyses will be performed on both the full analysis set (FAS) and the per-protocol set (PPS), with a *p*-value of less than 0.05 (two-tailed) is viewed as statistically significant.

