For the treatment and long-term management of AD, skin barrier repair and maintenance are essential. Guidelines for AD treatment suggest that appropriate bathing can facilitate the repair of skin lesions (12, 13). Previous studies indicate that various bath solutions can efficiently restore skin barrier function and increase skin hydration (40, 41). A meta-analysis has demonstrated that traditional Chinese herbal bath solutions can effectively alleviate clinical pruritus (42). MSS, as a weakly acidic solution containing over seven core Chinese herbal components, helps inhibit inflammation and preserve skin barrier integrity (43). Numerous studies have demonstrated that the core Chinese herbal components can exert anti-inflammatory effects through three key pathways: inhibiting the release of inflammatory mediators, regulating immune cell activity, and reducing oxidative stress (44–46). By inhibit inflammation, repairing the barrier, alleviating symptoms, and expediting recovery, this herbal bath solution anticipated to substantially improve clinical outcomes in AD patients. Additionally, this study design includes foundational therapies (desonide cream for mild AD and triamcinolone acetonide cream for moderate AD) alongside rescue medication (levocetirizine tablets for severe pruritus, 1 tablet each day), ensuring that all AD patients receive standardized background care throughout the trial.

Results in this study are expected to provide new insights and approaches for the prevention and treatment of AD. To our knowledge, this study is the first clinical trial to assess the clinical efficacy and safety of a traditional Chinese medicine solution combined with foundational therapies in the treatment of mild-to moderate AD. The evaluation will be conducted through a multidimensional approach, encompassing assessments of skin lesion severity, intensity of pruritus, and overall quality of life. The results of this study will provide robust evidence for the incorporation of traditional Chinese herbal bath solutions into clinical practice as a supplementary treatment modality for AD, thereby effectively facilitate long-term management of AD. We are planned to disseminate our findings through publication in internationally peer-reviewed journals.

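### Patients withdrawn for emergency treatment of worsening AD are imputed as missing at random, so a documented failure can be counted as an EASI50 responder

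*Protocol article*

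**What the plan says.** All references are to the protocol article.

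- **Primary outcome:** "The primary outcome indicator in this study is the EASI_50_ achievement rate at week 4". EASI is scored at weeks 0, 1, 2, 4 and 16.
- **Interventions:** "In this study, no additional treatment is permitted", and "emergency interventions require documentation in detail and will result in the withdrawal of participation". The corticosteroid cream is specified for 2 weeks and the urea ointment for 4 weeks. The study product runs for 4 months, and the ban on additional treatment has no stated end.
- **Statistical analysis:** the analysis follows ITT, "including all randomized participants regardless of adherence to the protocol or completion of the study". For gaps, "Missing data will be addressed under the missing-at-random assumption using sequential regression multiple imputation", using regression on the other variables. No reason for missingness is treated differently.
- **Discussion:** the design is said to include "rescue medication (levocetirizine tablets for severe pruritus, 1 tablet each day", which does not agree with the Interventions section.

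Nothing in the article provides for outcome assessment after withdrawal, or says how a withdrawn patient counts for EASI50.

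**The concern.** Two stated rules work against each other. The first turns a need for emergency treatment into missing data: a patient withdrawn before week 4 has no week-4 EASI. The second fills that gap from the observed relationships among variables, and these come mainly from patients who needed no such treatment. If the emergency was a worsening of AD, the trial has recorded why the patient left and that the course was bad, and then analyses the patient on a hypothetical course. This sits badly with the ITT principle stated in the same section, and it touches the primary endpoint.

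Week 16 is probably more exposed. No foundational therapy is specified after week 4, and the only later visit is week 16. A patient withdrawn in between is imputed mainly from values at weeks 1 to 4, taken during or just after the foundational therapy. The result then describes outcomes as if nobody had needed emergency treatment.

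The arms are small. One reclassified patient moves the control rate by 1/22 = 4.5 points and the treatment rate by 1/44 = 2.3 points.

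**Working it through.** **Inputs from the article (Sample size):** EASI50 rates "would be 85% in the treatment group and 50% in the control group"; two-sided α 0.05; power 80%; 2:1 allocation; 40 + 20 evaluable; 10% dropout; 44 + 22 enrolled. **Assumed:** the share w of each arm withdrawn for AD emergencies before week 4, which the article does not give.

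**1. The plan's own figure.** The printed formula with k = 2 gives n₂ = [(0.85 × 0.15)/2 + 0.50 × 0.50]/0.35² × (1.960 + 0.842)² = 0.31375/0.1225 × 7.849 = 20.1, and n₁ = 40.2. The stated 20 and 40 are reproduced, and 10% added gives 22 and 44. The sample size is not in dispute here.

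**2. Effect on the rates if 85% and 50% already count withdrawn patients as failures.** Imputing them at the rate of the patients who stay gives p/(1 − w) in each arm.

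| Withdrawn, treatment / control | Imputed rates | Difference (true: 35 points) |
|---|---|---|
| 5% / 5% | 89.5% vs 52.6% | 36.8 |
| 10% / 10% | 94.4% vs 55.6% | 38.9 |
| 10% / 15% | 94.4% vs 58.8% | 35.6 |
| 5% / 15% | 89.5% vs 58.8% | 30.7 |
| 5% / 20% | 89.5% vs 62.5% | 27.0 |

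Both rates rise in every row. The bias in the difference is 0.85·w_T/(1 − w_T) − 0.50·w_C/(1 − w_C). With equal withdrawal it is positive, because the treatment arm lends its failures a higher response rate. With w_T = 10% it stays positive until w_C passes about 15.9% (0.85 × 0.1111/0.50 = 0.1889; 0.1889/1.1889 = 0.159). The rows with 15% or 20% of controls withdrawn exceed the article's 10% dropout allowance and serve only to show that the sign can change.

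**3. Do earlier EASI values remove the problem?** An illustrative simulation assumed a log-EASI SD of 0.6, visit correlations of 0.5 to 0.7, the patients with the worst week-4 values withdrawn after week 2, and imputation from weeks 1 and 2. It credited about 60–70% of withdrawn treatment failures and 19–27% of withdrawn control failures as responders. With 10% withdrawn per arm, the imputed rates were about 92% vs 53% against true rates of 85% vs 50%, a difference of about 39 points. Applied to the 5%/15% row, the same crediting shares give 0.85 + 0.05 × (0.60 to 0.70) = 88.0–88.5% and 0.50 + 0.15 × (0.19 to 0.27) = 52.9–54.1%, a difference of about 34 to 36 points rather than 30.7.

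**4. Cost of counting withdrawn patients as failures, on the other basis.** Suppose 85% and 50% are instead the rates among patients who stay, and 10% per arm are withdrawn failures. The rates become 0.85 × 0.9 = 76.5% and 0.50 × 0.9 = 45.0%, a difference of 31.5 points. Exact power with 44/22 is 73.5% by chi-square and 65.9% by Fisher's test. Steps 2 and 4 rest on different readings of 85%/50% and must not be combined. On the reading of step 2, counting failures costs no power against the design assumption.

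**The case against.** **The text does not say that these are treatment failures.** This stands. The withdrawal rule covers emergency interventions of any kind, and an intolerance reaction or an unrelated event would fit it. A reader might infer that everyone withdrawn under the rule is a known AD failure; the article does not support that, so the point is limited to interventions for worsening AD.

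**Missing at random may be adequate, because EASI, VAS, IGA and DLQI at weeks 1 and 2 inform the imputation.** This stands in part. A patient already worsening at week 2 is not imputed simply as one who stayed, so the rates in step 2 are upper bounds for each arm (not for the difference). How far the assumption fails depends on when deterioration occurs. The simulation withdraws the worst week-4 patients, so it has the failure built in and shows possibility, not likelihood.

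**The bias might be thought to favour whichever arm withdraws more.** This is tempting and wrong. Equal 10% withdrawal raises the difference, and 10%/15% still raises it slightly although control loses more.

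**A separate analysis plan could define emergency treatment as non-response.** It could, and that would not contradict the article, since the outcome would then be defined rather than missing. But the published text already fixes imputation for missing data without exception, together with the withdrawal rule that makes the assumption doubtful for these patients. This is a stated rule that can give a wrong result, not an omitted detail.

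**Few such withdrawals are likely by week 4** in mild-to-moderate disease on background therapy. That is fair. The article gives no rate, so the size at week 4 may be small.

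**Conclusion.** The concern holds for patients withdrawn because of an emergency intervention for AD before an assessment. The plan documents the event, provides for no later data and can then impute a responder. Relative to counting such patients as failures, each arm's EASI50 rate is biased upward. The bias in the difference has no fixed size or sign: under the step 2 assumptions, 10% withdrawn per arm moves it from 35 to 39 points, which is an extreme case, and heavier control withdrawal can reverse it. The effect is likely larger at week 16, which carries secondary outcomes. The document does not support the stronger readings that all emergency withdrawals are AD failures, that the data are certainly not missing at random, or that the primary result is biased by a known amount or in a known direction. The conflict between the Interventions and Discussion sections matters here because it decides whether levocetirizine use leads to withdrawal, and so how many patients are affected.

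**What to change.** 1. In the primary EASI50 analysis, count a patient withdrawn for an emergency intervention for AD before the assessment as a non-responder. Keep multiple imputation for gaps unrelated to lack of efficacy. Do not extend the non-response rule to every rescue user: that would catch levocetirizine taken for itch, and pruritus is not an EASI component.
2. Report missing-at-random imputation of all gaps as a sensitivity analysis.
3. Where consent allows, continue the scheduled outcome visits after such withdrawal and use those data under ITT for the EASI, VAS, IGA and DLQI scores.
4. Reconcile the Interventions section (no additional treatment) with the Discussion (levocetirizine as rescue medication). Which of the two should stand is a clinical matter for the sponsor and the investigators.

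**Cost.** Items 1 and 2 are wording, with a slightly lower response rate and possibly lower power (about 73% by chi-square under step 4). Item 3 changes the withdrawal rule and needs an amendment reported to the ethics committee. It is also urgent: recruitment began in August 2025, and values not collected after withdrawal cannot be recovered.

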### Ethical considerations

This clinical trial protocol received approval from the Cosmetic Ethics Committee of Shanghai Skin Disease Hospital (2025-03) and is registered with the International Traditional Medicine Clinical Trial Registry (ITMCTR2025001206). This study will be conducted in strict accordance with the ethical principles outlined in the Declaration of Helsinki. Any adverse events, protocol violations, or amendments to the study protocol or informed consent form will be reported to the Cosmetic Ethics Committee. Written informed consent will be collected from all participants prior to their involvement in this study, and all signed consent forms and completed CRF will be securely stored in a locked location, accessible only to authorized study personnel.

## Results

In this study, ethical approval was granted in March 2025, with registration completed in the International Traditional Medicine Clinical Trial Registry in June 2025. Recruitment of patient began in August 2025 and is anticipated to be concluded by June 2026. Data analysis is set to start in August 2026, submission of the preliminary trial results for peer review is anticipated by the end of December 2026.

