## Methods

### Study design

This randomized, double-blind, placebo-controlled trial is designed to evaluate the efficacy of MSS combined with foundational therapies in improving skin lesions and relieving pruritus in patients with mild-to-moderate atopic dermatitis (AD). The study protocol adheres to the SPIRIT (Standard Protocol Items: Recommendations for Interventional Trials) guidelines (20). A total of 66 patients with mild-to-moderate AD will be enrolled at the Shanghai Skin Disease Hospital during August 2025 and June 2026. Patients will be randomly assigned in a 2:1 ratio to either the treatment group (MSS combined with foundational therapies, *n* = 44) or control group (MSS placebo combined with foundational therapies, *n* = 22). The study flowchart is shown in Figure 1.

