### Blinding

In this study, both of patients with mild-to-moderate AD and dermatologists will be blinded to the treatment allocation. Additionally, outcome assessors, data collectors, and statisticians responsible for data analysis will also remain unaware of the group assignments throughout the trial period to prevent potential information bias.

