#### Secondary outcomes

The secondary outcome indicators include the EASI, Visual Analogue Scale (VAS), Investigator’s Global Assessment (IGA), and Dermatology Life Quality Index (DLQI) (23, 24). These indicators will be assessed at baseline (week 0) and subsequently at weeks 1, 2, 4, and 16. A detailed study schedule is presented in Table 1, which specifies the evaluation time points for each measure.

**Table 1 tab1:** Study schedule of the MuShengshu clinical trial (16 weeks).

Indicator	Baseline	Follow-up			
	Visit 1 (week 0)	Visit 2 (week 1)	Visit 3 (week 2)	Visit 4 (week 4)	Visit 5 (week 16)
Informed consent	✓	–^a^	–	–	–
Demographic features	✓	–	–	–	–
Family medical history	✓	–	–	–	–
Physical examination	✓	–	–	–	–
Inclusion/exclusion criteria check	✓	–	–	–	–
Randomization	✓	–	–	–	–
EASI^b^	✓	✓	✓	✓	✓
VAS^c^	✓	✓	✓	✓	✓
IGA^d^	✓	✓	✓	✓	✓
DLQI^e^	✓	✓	✓	✓	✓
Concomitant medications	–	✓	✓	✓	✓
Adverse events	–	✓	✓	✓	✓

a Not applicable.

b EASI: Eczema Area and Severity Index.

c VAS: Visual Analogue Scale.

d IGA: Investigator’s Global Assessment.

e DLQI: Dermatology Life Quality Index.

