This study is subject to several limitations. First, patients recruitment is restricted to individuals with mild-to-moderate AD enrolled at the Shanghai Skin Disease Hospital, which enhancing internal validity while potentially limiting the generalizability of findings. Second, the protocol outlined a follow-up period lasting up to 4 months, which may result in patient dropout and lead to missing data and potentially impact the accuracy of the study’s findings. Thirdly, the study design, with a four-month follow-up, does not allow for evaluation of the long-term effects of MSS bath solution on AD recurrence rates. Therefore, it is essential to conduct a more relevant multi-center, randomized, placebo controlled clinical trials in the future.

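### The stated analysis start of August 2026 falls before the last week-16 visits if recruitment runs to June 2026; the dates must be reconciled

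*Protocol article*

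**What the plan says.** The article fixes four things that bear on the calendar.

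- **Recruitment.** The Results section states "Recruitment of patient began in August 2025 and is anticipated to be concluded by June 2026". The abstract and the Study design section give the same window for all 66 patients ("will be enrolled at the Shanghai Skin Disease Hospital during August 2025 and June 2026").
- **Treatment and follow-up.** Under Interventions, "Patients in the treatment group will take a daily bath using MSS for a period of 4 months", and the control group uses the placebo for the same time. Under Secondary outcomes, "These indicators will be assessed at baseline (week 0) and subsequently at weeks 1, 2, 4, and 16". Table 1 also places the last record of adverse events and concomitant medications at week 16.
- **Analysis.** In the Results section, and likewise in the abstract, "Data analysis is set to start in August 2026". Submission of preliminary results is expected by the end of December 2026.
- **Blinding.** Besides patients and dermatologists, the outcome assessors, data collectors and analysing statisticians "will also remain unaware of the group assignments throughout the trial period to prevent potential information bias".

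On the endpoint itself: "The primary outcome indicator in this study is the EASI_50_ achievement rate at week 4".

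**The concern.** The last patients recruited need 16 weeks of follow-up, but the gap between the end of recruitment and the start of analysis is two months at most on the stated dates (1 or 30 June to August). Nothing in the article limits the August analysis to week 4 or otherwise says which data it uses.

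Taken literally, an August start has one of two consequences. Either the week-16 data of the latest recruits are not in the analysis, or groups are compared while some patients are still being treated and scored. EASI and IGA are rated by investigators, and VAS and DLQI by patients, so knowledge of results at a single centre could affect the remaining scores. Masked group labels would protect little here: with 2:1 allocation, group sizes of 44 and 22 show the analyst which arm is which.

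Week 16 is the only assessment after week 4. It carries all later efficacy and safety information behind the article's interest in long-term management.

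**Working it through.** The plan derives no figure for this timeline, so the check starts from its stated dates.

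**Inputs.** Recruitment August 2025 to June 2026 and 66 patients (Study design, Results); primary endpoint at week 4 = 28 days (Primary outcome); last visit at week 16 = 112 days (Secondary outcomes, Table 1); analysis start August 2026 (abstract, Results). Days within each month are not given, so the first and last days are used as bounds.

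**Step 1: visit dates = enrolment date + 28 or + 112 days.**

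| Enrolled | Week 4 | Week 16 |
|---|---|---|
| 1 June 2026 | 29 June 2026 | 21 September 2026 |
| 15 June 2026 | 13 July 2026 | 5 October 2026 |
| 30 June 2026 | 28 July 2026 | 20 October 2026 |

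Week 4 is complete before August in every case. Week 16 is not complete in August for anyone enrolled in June.

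**Step 2: the gap.** Shortest: 31 August to 21 September = 21 days = 3 weeks. Longest: 1 August to 20 October = 80 days = 11.4 weeks.

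**Step 3: latest enrolment compatible with an August start.** 1 August 2026 − 112 days = 11 April 2026. 31 August 2026 − 112 days = 11 May 2026. No August date fits recruitment into June.

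**Step 4: patients affected.** This assumes even accrual, which the article does not state. The share not yet at week 16 = (last enrolment − latest compatible enrolment) / (last enrolment − first enrolment), and the number is 66 × share.

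| First enrolment | Last enrolment | Analysis start | Share | Patients |
|---|---|---|---|---|
| 1 Aug 2025 | 1 June 2026 | 31 Aug 2026 | 21/304 = 6.9% | 4.6 |
| 31 Aug 2025 | 1 June 2026 | 31 Aug 2026 | 21/274 = 7.7% | 5.1 |
| 1 Aug 2025 | 30 June 2026 | 31 Aug 2026 | 50/333 = 15.0% | 9.9 |
| 31 Aug 2025 | 30 June 2026 | 31 Aug 2026 | 50/303 = 16.5% | 10.9 |
| 1 Aug 2025 | 1 June 2026 | 1 Aug 2026 | 51/304 = 16.8% | 11.1 |
| 31 Aug 2025 | 1 June 2026 | 1 Aug 2026 | 51/274 = 18.6% | 12.3 |
| 1 Aug 2025 | 30 June 2026 | 1 Aug 2026 | 80/333 = 24.0% | 15.9 |
| 31 Aug 2025 | 30 June 2026 | 1 Aug 2026 | 80/303 = 26.4% | 17.4 |

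The range is about 5 to 17 of 66 patients.

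**Step 5: room before submission.** 20 October to 31 December 2026 = 72 days, about ten weeks.

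**The case against.** The strongest reply is that the article gives only a month in which analysis begins, inside a forecast timeline. It does not say that allocation is opened in August, that groups are compared then, or that data are locked without week 16. Other sections point the other way: data are to be entered for all 66 participants, all randomized participants are to be analysed, and statisticians stay blinded. Blinded preparatory work could begin in August and finish after October, or August could concern week 4 only. A December submission leaves time for a complete analysis. Recruitment could also end before June.

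Most of this stands, and it limits the point. A reader might infer that the plan intends to analyse an incomplete trial or to break the blind early. The documents do not support that: it would require acting against the Blinding section, and no sentence announces it. Nor does the Statistical analysis section say that visits still pending would be imputed.

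A reader might also set the 5 to 17 pending patients against the 10% dropout allowance. That comparison fails, because the allowance belongs to the week-4 sample size, and visits pending because of late enrolment are not dropout. They imply no loss of power for the primary endpoint.

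The date conflict itself survives. The benign readings are possible, but the article states none of them. This is also not detail that an article may leave to a fuller document, because the August date is printed twice and conflicts with the recruitment window and follow-up printed beside it.

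**Conclusion.** The point holds as an inconsistency of dates, of moderate severity. An August 2026 analysis start cannot include complete week-16 data if recruitment continues into June 2026; the shortfall is about 3 to 11 weeks.

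The effect is confined to the week-16 secondary and safety data and to the protection of blinding until follow-up ends. The week-4 primary endpoint and the sample size that rests on it are untouched.

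The visit dates follow from the stated schedule, with no visit window added. The count of patients affected also rests on even accrual and on unknown days within the stated months. If recruitment closed by 11 May 2026, a start on 31 August would be possible and the conflict would disappear.

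**What to change.** Amend the timeline in the abstract and in the Results section together, in one of two ways.

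1. Place database lock, unblinding and between-group analysis after the last patient's week-16 visit, which means after about 20 October 2026 if recruitment runs to 30 June. This is the simpler option.
2. State that the August analysis covers week 4 only, and that arm-level results are withheld from patients, assessors and data collectors until the last week-16 visit. The Blinding section should then say how this fits with statisticians remaining blinded throughout the trial period.

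The first option costs a delay of about 2 to 3 months including data cleaning, with no added patients or procedures. It leaves about ten weeks between the last possible visit and the end of December 2026, so the planned submission becomes tighter but stays feasible. The second keeps the August date but needs explicit access rules. Either should be settled before any between-group comparison starts, because unblinding cannot be undone.
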